# Multicentre, national, investigator-initiated, randomised, parallel-group, register-based superiority trial to compare extended ECG monitoring versus standard ECG monitoring in elderly patients with ischaemic stroke or transient ischaemic attack and the effect on stroke, death and intracerebral bleeding: the AF SPICE protocol

**DOI:** 10.1136/bmjopen-2023-073470

**Published:** 2023-11-23

**Keywords:** Stroke, Cardiology, Thromboembolism

## Abstract

**Introduction:**

Atrial fibrillation (AF) is a major risk factor for ischaemic stroke and transient ischaemic attack (TIA), and AF detection can be challenged by asymptomatic and paroxysmal presentation. Long-term ECG monitoring after ischaemic stroke or TIA is recommended by all major societies in cardiology and cerebrovascular medicine as a secondary prophylactic measure. However, data on stroke reduction are lacking, and the recommendations show significant diversity.

**Methods and analysis:**

AF SPICE is a multicentre, national, investigator-initiated, randomised, parallel-group, register-based trial comparing extended ECG monitoring versus standard ECG monitoring in patients admitted with ischaemic stroke or TIA, with a composite endpoint of stroke, all-cause-mortality and intracerebral bleeding. Patients aged ≥70 years without previous AF will be randomised 1:1 to control (standard ECG monitoring) or intervention (extended ECG monitoring). In the control arm, patients will undergo 48±24 hours (ie, a range of 24–72 hours) of continuous ECG monitoring according to national recommendations. In the intervention arm, patients will undergo 14+14 days of continuous ECG monitoring 3 months apart using an ECG patch device, which will provide an easy-accessed, well-tolerated 14-day continuous ECG recording. All ECG patch recordings will be read in a core facility. In cases of AF detection, oral anticoagulation will be recommended if not contraindicated. A pilot phase has been concluded in 2022, which will transcend into the main trial during 2023–2026, including approximately 30 stroke units. The sample size was calculated to be 3262 patients. The primary outcome will be collected from register data during a 36-month follow-up.

**Ethics and dissemination:**

Ethical approval has been provided by the Swedish Ethical Review Authority, reference 2021–02770. The trial will be conducted according to the ethical principles of the Declaration of Helsinki and national regulatory standards. Positive results from the study have the potential for rapid dissemination in clinical practice.

**Trial registration number:**

NCT05134454.

STRENGTHS AND LIMITATIONS OF THIS STUDYFirst register-based randomised clinical trial on secondary preventive ECG screening poststroke/transient ischaemic attack with stroke and all-cause mortality endpoints.Participants were included from a national network of stroke units and central adjudication of ECG recordings in the intervention arm.Robust inclusion criteria mirror the clinical real-world population; age at least 70 years for inclusion.The Swedish stroke register (Riksstroke) is used for the provision of the majority of baseline data.Endpoints from healthcare registers will not be further adjudicated.

## Introduction

Ischaemic stroke is one of the leading causes of mortality worldwide and a major cause of permanent disability in adults.^1^ Despite the implementation of novel treatment strategies, morbidity and mortality remain significant.

Modifiable risk factors for stroke include hypertension, atrial fibrillation (AF), hyperlipidaemia, smoking and diabetes.^2 3^ Several of these risk factors have been undetected for a long time since they remain asymptomatic.

During 2018, the stroke incidence in Sweden was 223 per 100 000 in men and 191 per 100 000 in women.^4^ At the 3-month follow-up poststroke, 26% were deceased or dependent on activities of daily living.^4 5^ The risk for stroke recurrence is highest during the first 3–6 months following admission, and the 1-year recurrence risk has been reported to be 3–5%.^6 7^

The societal burden of the disease is significant. Disability with a need for long-term care, and in younger patients, impaired work ability entails enormous societal costs.^8^ Strokes due to AF are more severe and have significantly higher mortality than other stroke cases.^9^

AF is the most prevalent clinical arrhythmia, with a steeply increasing incidence with advancing age.^10^ AF is also one of the strongest risk factors for stroke.^3^ However, the increased stroke risk associated with AF can be markedly reduced by oral anticoagulation (OAC) treatment.^11^ Unfortunately, AF is paroxysmal and asymptomatic in a significant proportion of stroke patients, leading to lower detection rates and frequently leaving stroke survivors with an undiagnosed and untreated risk factor and a higher risk of stroke recurrence.^12^ Despite this, no study so far has reported evidence of the benefit of ECG AF screening in terms of reduced stroke recurrence and mortality after a stroke event.

Randomised controlled trials^13^ (CRYSTAL-AF^14^ and EMBRACE^12^) have shown that prolonged ECG monitoring compared with standard of care (at the time of 24-hour ECG) increased detection of AF in patients with cryptogenic stroke.

The FIND-AF_randomised_ trial^15^ also showed increased detection of AF and included a broader group of participants, suggesting that prolonged ECG monitoring should be used in all patients with ischaemic stroke.

The MonDAFIS study^16^ was powered to evaluate the proportion of anticoagulation therapy 12 months after index stroke. The standard of care was compared with prolonged inhospital ECG monitoring (maximum 7 days). AF detection was increased in the intervention group, but this had no significant effect on the rate of anticoagulation therapy at 12 months.

AF screening after an ischaemic stroke event is currently recommended by major international societies (table 1).^17–23^ The recommendations vary markedly with respect to the method of screening and duration of screening. There is, however, a body of data on the proportion of AF detection using different monitoring strategies.^24^

**Table 1 T1:** ECG screening poststroke society recommendations

Society	Recommendation summary	Year	Ref
European Stroke Organisation	In adult patients with ischaemic stroke or TIA of undetermined origin, we recommend a prolonged cardiac monitoring instead of standard 24 hours monitoring to increase the detection of subclinical AF. In adult patients with ischaemic stroke or TIA of undetermined origin, we recommend longer duration of cardiac rhythm monitoring of more than 48 hours and if feasible with n implantable loop recorder to increase the detection of subclinical AF.	2022	21
American Heart Association/American Stroke Association	In patients suspected of having a stroke or TIA, an ECG is recommended to screen for AF and atrial flutter and to assess for other concomitant cardiac conditions. In patients with cryptogenic stroke who do not have a contraindication to anticoagulation, long-term rhythm monitoring with mobile cardiac outpatient telemetry, an implantable loop recorder or other approach is reasonable to detect intermittent AF.	2021	19
European Society of Cardiology	In patients with acute ischaemic stroke or TIA and without previously known AF, monitoring for AF is recommended using a short-term ECG recording for at least the first 24 hours, followed by continuous ECG monitoring for at least 72 hours whenever possible. In selected stroke patients without previous known AF, additional monitoring using long-term non-invasive ECG monitors or insertable cardiac monitors should be considered to detect AF.	2020	18
Swedish board of health and welfare	Healthcare should provide a long-term ECG for 24–48 hours. long-term ECG for more than 48-hour duration using Holter recording or inpatient telemetry ECG in selected cases.	2020	
NICE	Reveal LINQ is recommended as an option to help to detect AF after cryptogenic stroke only if: non-invasive ECG monitoring has been done and a cardiac arrhythmic cause of stroke is still suspected.	2020	15
Canadian Cardiovascular Society/Canadian Heart Rhythm Society	We recommend at least 24 hours of ambulatory ECG monitoring to identify AF in patients with non-lacunar ESUS. We suggest additional monitoring for AF detection (eg, prolonged external loop recorder or implantable cardiac monitoring, where available) be performed for selected older patients with non-lacunar ESUS in whom AF is suspected but unproven.	2020	16
National Heart Foundation of Australia and the Cardiac Society of Australia and New Zealand	Screening for AF in patients with ESUS recommendation: for patients with ESUS, longer term ECG monitoring (external or implantable) should be used.	2018	17
Royal College of Physicians	People with ischaemic stroke or TIA who would be eligible for secondary prevention treatment for AF (anticoagulation or left atrial appendage device closure) should undergo a period of prolonged (at least 12 hours) cardiac monitoring. People with ischaemic stroke or TIA who would be eligible for secondary prevention treatment for AF and in whom no other cause of stroke has been found should be considered for more prolonged ECG monitoring (24 hours or longer), particularly if they have a pattern of cerebral ischaemia on brain imaging suggestive of cardioembolism.	2016	20

AF, atrial fibrillation; ESUS, embolic stroke of uncertain source; TIA, transient ischaemic attack.

The development of ECG modalities and clinical practice for AF screening postischaemic stroke and TIA have evolved towards longer and more resource-demanding investigations, as noted in table 1, despite the lack of data on clinical endpoints like stroke. Diversity within recommendations has promoted unequal care even within countries and regions. With this background, there is an urgent need for a randomised trial to investigate the efficacy of secondary prophylactic AF screening following ischaemic stroke.

### Choice of comparators

In some of the recommendations on AF screening for postischaemic stroke from international societies, a basic monitoring duration of 24 hours of continuous ECG is recommended.^18 20^ In the recommendations from the Swedish Board of Health and Welfare, continuous ECG monitoring of 24–48 hours is recommended as the baseline investigation for patients with ischaemic stroke patients, and a large share of stroke units in Sweden adhere to this recommendation.

## Methods and analysis

### Primary objectives

To determine if extended continuous ECG screening (14+14 days) is superior to standard ECG screening (48±24 hours, that is, range 24–72 hours) in reducing the risk of the combined endpoint of ischaemic stroke, intracerebral bleeding and all-cause mortality in elderly patients admitted to the hospital for ischaemic stroke or TIA.

### Key secondary objectives

The key secondary objectives are to estimate the treatment effect on the primary outcome and determine if there are any differences between extended and standard ECG screening for:

Ischaemic stroke.All-cause mortalityIntracranial bleedingMajor bleeding.Myocardial infarction.Pacemaker implantation.Cost-effectiveness.

### Other secondary objectives

To study the association between age and AF detection.To study the proportion of other relevant arrhythmias detected at ECG screening.To study predictors for AF detection.To study signal time and signal quality achieved at ECG screening.To study long-term adherence to OAC treatment.To study the feasibility of patients’ application of the second ECG patch.To study patient reported experience, collected 3 months after inclusion in the main trial.Per protocol analysis of the primary outcome.Win ratio analysis.

### Trial design

AF SPICE is designed as a multicentre, national, investigator-initiated, randomised, parallel-group, register-based superiority trial to compare extended ECG monitoring versus standard ECG monitoring in elderly patients admitted with ischaemic stroke or TIA with the combined endpoint of recurrent ischaemic stroke, all-cause mortality and intracerebral bleeding (figure 1).

**Figure 1 F1:**
[figure not shown]
Overview of study design, AF SPICE.

### Study setting

AF SPICE will recruit participants among admissions for ischaemic stroke or TIA in stroke units in Swedish hospitals. Inclusion is also possible from non-stroke units given that the patient is admitted for ischaemic stroke or TIA and identified by the site’s local investigator or delegate.

A pilot trial commenced in January 2022 and is now concluded, converting into the main study in 2023. The pilot trial evaluated inclusion rates, feasibility and adherence to ECG recorders and the database with a randomisation system.

### Eligibility criteria

#### Inclusion criteria

Patients aged ≥70 years admitted to a stroke unit with a diagnosis of ischaemic stroke or TIA within 14 days of inclusion. Stroke is clinically defined as the acute onset of a focal neurological deficit of presumed vascular origin lasting for ≥24 hours or resulting in death. Stroke is further categorised as ischaemic or as intracerebral or subarachnoid haemorrhage based on CT and/or MRI of the brain. TIA is defined as a sudden, focal neurological deficit of presumed vascular origin with transient symptoms (<24 hours).^25^ Only patients with ischaemic stroke and TIA are eligible for inclusion.Signed informed consent.

#### Exclusion criteria

Previously diagnosed AF.Contraindication to OAC treatment.Indication for anticoagulant treatment other than AF.Patients with a pacemaker, implantable cardioverter defibrillator or implantable loop recorder.Patients who, according to the investigator, will not be able to comply with the trial protocol.Previous participation in the AF SPICE trial.

The rationale for the age cut-off of 70 years in AF SPICE is partly due to the higher AF yield in elderly patients, as well as the increased benefit of OAC treatment in elderly patients in the case of AF detection. Notably, 74% of stroke patients in Sweden are aged 70 years or older, making the study population quite representative of future implementation. The recruitment window of 14 days is intended to give a margin for the occurrence of patient transfers between centres for thrombectomy, holidays and uncertainty about eligibility. Patients with a cardiac implantable device are excluded since their very long-lasting continuous heart rhythm monitoring will make them biased with a lower probability of AF detection on a surface ECG recording. Further, ventricular pacing will make reading the patch ECG difficult due to the lack of pacing annotations.

#### Withdrawal of patients

A patient can withdraw from the trial at any time, at the discretion of the patient, or by the investigator if deemed medically indicated. If a participant refrains from completing the extended ECG recording protocol, he/she will remain included in the trial and in the intention-to-screen data analysis. A withdrawal of consent means that no further trial data will be collected; however, already collected data will not be erased.

#### Patient and public involvement

Patient or public involvement is planned but not yet in place in this trial.

#### Procedures for handling arrhythmias detected on extended ECG recordings

AF is defined according to the current definition of the ESC AF guidelines,^20^ that is, at least 30 s with irregular R-R intervals, the absence of distinct repeating p-waves and irregular atrial activations. When this is met, the local investigator will be notified within one working day by phone and email by the ECG reading team.

If a participant is diagnosed with other arrhythmias with a prognostic implication as defined in box 1, the local investigator will be notified by email within three working days. However, due to the high prevalence of ventricular arrhythmias during 14 days of continuous ECG in this population, a selection based on team discussion is made for ventricular tachycardia. If more rapid action is deemed necessary by the ECG reading team, appropriate measures will be undertaken. When no significant arrhythmias are noted, the local investigator will be notified within 1 week of the ECG upload.

Box 1Prognostic ECG findings on extended ECG recording which should be communicated to the local investigator.Ventricular tachycardia.Excessive ventricular extrasystoles (>5%).Pause >3 s.AV block types II and III.Bradycardia <40/minute.

#### Procedures for poor signal quality and short recordings in extended ECG

If the signal quality of the extended ECG recording is deemed to be insufficient, the participant should be offered another patch ECG recording. If this second recording has insufficient signal quality or if it is not possible to arrange for another patch ECG recording, a traditional Holter recording or an ECG event recording could be used. However, it is important for the power of the trial to achieve as long ECG recordings as possible in the intervention group.

At least 7 days of ECG recording should be yielded from the ECG patch on visit one. If less than 7 days are recorded, another recording should be offered. The same minimum ECG duration of 7 days applies for ECG recording at visit two.

If a participant randomised to the intervention arm with a negative ECG recording (ie, no AF detected) suffers a recurrent ischaemic stroke within 2 months from visit one, the second ECG patch recording (visit two) may be started earlier than 2 months, to the discretion of the local investigator.

#### OAC initiation following AF detection in extended ECG recording

Patients diagnosed with AF during the long-term ECG recordings initiated in connection with randomisation should be informed by the local investigator and offered treatment with OAC if there are no contraindications, based on the stroke risk of at least CHA_2_DS_2_-VASc three points in randomised patients.

Treatment with OAC and its long-term follow-up will be handled within standard care and according to national guidelines.

When indicated, OAC treatment should be initiated within five working days from the reception of long-term ECG results. Long-term follow-up of OAC treatment will be done using the national drug prescription registry.

All other treatments and investigations will be at the discretion of the local investigator.

#### Standard care

Participants randomised to standard care should undergo 48±24 hours of continuous ECG monitoring, using inpatient ECG telemetry monitoring or Holter recording. The duration of the monitoring should be recorded by the site and noted in the electronic case report form (REDCap, Vanderbilt University, TN, USA).

The trial will not collect any data from the standard recordings apart from its duration and containment of AF. ECG recordings of newly diagnosed AF in the standard care arm will be collected and stored in the trial.

### Outcomes

#### Primary endpoint

Difference between the two arms in a combined endpoint of recurrent ischaemic stroke, intracerebral bleeding and all-cause mortality during at least 36 months of follow-up.

#### Secondary endpoints

Individual components of the primary endpoint.Major bleeding, including intracranial bleeding.Myocardial infarction.Pacemaker implantation.Anticoagulation treatment.AF prevalence.Adherence to long-term ECG recording.Incidence of other prognostic arrhythmias during long-term ECG recording.

#### Participant timeline: intervention arm

Participants will be screened for consent during admission for ischaemic stroke or TIA, within 14 days of admission. ECG investigation of 0–48 hours prior to randomisation is allowed. Extended ECG recording is initiated during admission for ischaemic stroke/TIA, and the participant will return the device via mail. The second extended ECG recording should be initiated at the follow-up visit or by mailing the device to the participants for self-application. Following completion of the second 14-day ECG recording, no further personal visits are made in the trial.

#### Participant timeline: standard arm

Starting or completing the ECG recording in the standard arm following discharge is allowed. Following completion of the ECG investigation initiated in the standard arm, no further personal visits are made in the trial.

#### Sample size

The sample size was calculated based on the primary outcome.

There were very few studies available with outcome data matching the age and morbidity of the AF SPICE trial. Very few studies on patients with an index stroke incident were available; in particular, there was a lack of data regarding patients with recent strokes and AF without OAC treatment. For this, we have made estimations and extrapolations using the very few available studies on patients with AF without OAC treatment. In particular, extrapolations have been made with regard to age since most available studies have included patients considerably younger than what is expected in AF SPICE. A list of studies used in sample size estimations is available in online supplemental appendix.

10.1136/bmjopen-2023-073470.supp1Supplementary data

For the estimations of AF detection proportions, available studies on short-term (48±24 hours) ECG recordings following stroke and corresponding studies on long-term (14 days) recordings were used. As with the outcome data, no studies with similar populations and ECG recording durations were available. Furthermore, the AF detection/incidence was estimated for the entire follow-up for both arms, reflecting the additional detection within standard care after the index event, thereby reflecting the actual risk exposure in both arms during follow-up. A list of the AF detection studies available for this estimation is reported in online supplemental appendix.

The assumptions for the sample size calculation are reported in table 2. The complete sample size calculation is provided in the appendix. For the yearly risk of the composite endpoint, we estimate 17% in patients with AF and no OAC treatment, 7.3% in patients with AF and OAC treatment and 5% risk in patients without AF. We further estimate an AF detection proportion of 6% in the control group and 19% after two ECG recordings in the intervention group, and 13% with untreated AF in the control group, resulting in a sample size of 2718 for 3 years of fixed follow-up time after inclusion. Adding 20% for participant dropouts and treatment discontinuation, a total sample size of 3262 is needed, corresponding to 1631 in each arm based on 3 years of follow-up, 80% power and a double-sided significance level of 5%. The study is powered to detect a 9% reduction in the composite endpoint in the group with extended ECG screening.

**Table 2 T2:** Event rates and AF detection rates used in sample size calculation

Endpoint* risk in patients with AF and OAC treatment	7.3%
Endpoint risk in patients with AF and no OAC treatment	17%
Endpoint risk in patients without AF	5%
AF detection proportion in standard arm†	6%
AF detection proportion in intervention arm†	19%

*Endpoint including recurrent stroke, all-cause mortality and intracerebral bleeding.

†Including AF detection during follow-up.

AF, atrial fibrillation; OAC, oral anticoagulation.

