#### ECG data

There are different ECG variables for the control and intervention arms (online supplemental appendix).

In the control arm, the local investigator or delegate will report if ECG was recorded using ECG telemetry and/or Holter recording, the duration of each recording and whether AF was diagnosed.In the intervention arm, ECG data from patch recordings will be stored in the patch hardware and returned by the participant by mail. Data from ECG patch hardware will be uploaded by the patch provider into the Cardiologs database. ECG patch data will be scrutinised by the core reading team, which also enters ECG data manually into the REDCap database.

For the second ECG patch recording initiated 2–4 months following randomisation, data will be collected on whether the patch is applied within healthcare or by the participant.

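### The 19% AF detection in the intervention arm has two time frames, and the printed sizing inputs carry no term for the delay before anticoagulation starts

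*Protocol article*

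**What the plan says.** All references are to the protocol article.

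- **Detection, first description (Sample size):** "19% after two ECG recordings in the intervention group".
- **Detection, second description:** earlier in the same section, "the AF detection/incidence was estimated for the entire follow-up for both arms", which the authors describe as "thereby reflecting the actual risk exposure in both arms during follow-up". The Table 2 footnote attached to both detection proportions reads "Including AF detection during follow-up".
- **Risks:** as yearly figures, "we estimate 17% in patients with AF and no OAC treatment, 7.3% in patients with AF and OAC treatment and 5% risk in patients without" (the last group being those free of the arrhythmia). Control is given 6% detected and 13% untreated AF.
- **Size:** 2718 for three years of fixed follow-up. It is raised by 20% to 3262, and the 20% is labelled for dropout and treatment discontinuation. The design is "based on 3 years of follow-up, 80% power and a double-sided significance level of 5"%. The complete calculation is referred to an appendix.
- **Schedule:** the first patch is applied at randomisation, worn for 14 days and mailed back (Extended ECG investigation). The site is told of AF within one working day of its identification (Procedures for handling arrhythmias). Anticoagulation should start within five working days of the result (OAC initiation). On the second patch, the ECG data section says "For the second ECG patch recording initiated 2–4 months following randomisation".
- **Analysis:** log-rank test on time to first event, by intention to treat (Statistical methods).

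**The concern.** Detection complete after two recordings closes at about month 5, whereas detection over the entire follow-up closes at month 36. If the second meaning holds, the patches find less than 19% and the rest is found, and treated, at some later time. A reader cannot tell which yield the trial needs. The data monitoring board is asked to review the yield of the ECG recordings and has no clear benchmark.

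On either meaning, the published inputs contain proportions and constant yearly risks but no time to treatment. A patient whose AF is found on the second patch carries the untreated risk for several months, and the log-rank test counts events from randomisation. Cumulative detection by month 36 is therefore not the same as treated exposure from month 0. If the calculation behind the printed inputs ignores this, the stated power does not describe the trial as scheduled. The Introduction adds a reason to care about the early months: "The risk for stroke recurrence is highest during the first 3–6 months following admission".

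**Working it through.** **1. What the inputs imply.** 6% + 13% = 19%, so every intervention-arm AF case is counted as detected and treated.

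- Control yearly risk: 0.06 × 7.3 + 0.13 × 17 + 0.81 × 5 = 6.698%.
- Intervention: 0.19 × 7.3 + 0.81 × 5 = 5.437%.
- Difference: 1.261 points.

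**2. The plan's own figure.** With these inputs, three fixed years, 80% power, two-sided 5% and no delay, the total required depends on how yearly risk is carried forward.

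| Method | N required | Power at 2718 |
|---|---|---|
| Linear | 3266 | 72% |
| Averaged risk, compounded | 3994 | 64% |
| Averaged risk, exponential | 4374 | 60% |
| Mixture of strata, compounded | 5156 | 53% |
| Mixture of strata, exponential | 6172 | 46% |

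None gives 2718. The 20% step does reproduce: 2718 × 1.2 = 3261.6, rounded to 3262.

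**3. Time to treatment from the schedule.** Patch 1: 14 days of wear, mailing, upload, reading, then up to five working days, so about month 1. Patch 2: start at month 2 to 4 plus the same steps, so about month 3 to 5. I use months 1 and 4. The share of patch-detected AF found by patch 2 is not given; I assume 20-35%.

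**4. Hand check of size and sign.**

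- Mean delay: 0.80 × 1 + 0.20 × 4 = 1.6 months, or 0.65 × 1 + 0.35 × 4 = 2.05 months.
- Full treatment contrast in the intervention arm: 0.19 × (17 − 7.3) = 1.843 points a year.
- Contrast lost over 36 months: 1.843 × 1.6/36 = 0.082 points, or 1.843 × 2.05/36 = 0.105 points. That is 6.5-8.3% of the 1.261-point difference.
- If 3 of control's 6 points are found on average at month 18, control's risk rises by 0.03 × 9.7 × 18/36 = 0.146 points, which more than offsets that loss. With 2 points it rises by 0.097, about break-even.
- Equal late detection raises both arms' risk alike, and so leaves the difference close to the no-late case.

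**5. Log-rank calculation.** Yearly risks are converted to hazards, −ln(1 − r). AF patients carry the 17% hazard until treatment and the 7.3% hazard afterwards; each arm is a mixture of strata. With Y the expected number at risk and λ the hazard in each arm,

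z = Σ [Y_C·Y_I/(Y_C+Y_I)]·(λ_C − λ_I)·dt ÷ √{Σ [Y_C·Y_I/(Y_C+Y_I)²]·events}.

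Without delay, at N = 2718: three-year risks 18.3% and 15.4%, z = 2.049. Unscaled, that is about 54% power, in line with the mixture row in step 2. To isolate timing, each scenario's z is taken relative to 2.049 and applied to the printed 80%: power = Φ(2.80 × z/2.049 − 1.96). Late detection is placed at month 18; spreading it evenly over follow-up changes the powers by less than one point.

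| Late detection, in points (part of the 6% and 19%) | z | Nominal 80% becomes |
|---|---|---|
| None in either arm | 1.83-1.88 | 71-73% |
| 2-4 in both arms | 1.84-1.89 | 71-73% |
| 3 control, 1 intervention | 2.00-2.05 | 78-80% |
| 2-4 control only | 2.00-2.22 | 78-86% |

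In these rows all patch-detected AF waits until month 1 or 4, while control's early-detected AF is treated from day 0. If instead 6 of the 19 points are treated from day 0 in both arms, through the standard monitoring, the first row becomes z = 1.90-1.93, or about 74-75%.

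**The case against.** The strongest reply has four parts.

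- **The two descriptions may be one.** The Sample size section says detection covers the entire follow-up before it gives 19%, and Table 2 repeats this. The later phrase may be shorthand for the arm that receives two recordings. This stands as far as it goes: the descriptions are different time frames that need reconciling, and to call them incompatible would be too strong.
- **Treatment from day 0 is not stated.** A reader might infer that the sizing credits anticoagulation from randomisation. The published inputs suggest it, but no formula is printed, the appendix is not at hand, and 2718 does not reproduce. The supported statement is that the printed inputs show no term for delay, so they do not support the claim about actual exposure. The 20% uplift is no answer, because it is labelled for other losses.
- **The loss is not certain.** A reader might conclude that the schedule cannot deliver the stated power. The section says control's 6% includes later detection in usual care. If 19% is purely the patch yield, late detection falls in control only and power may not drop at all. For the same reason the row with no late detection is a boundary case.
- **Higher early risk.** A reader might add a larger loss because recurrence is concentrated early. The Introduction gives a direction for stroke recurrence only. It gives no factor, and nothing for the full composite, which includes death. This belongs in a sensitivity analysis.

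It is also fair to say that the failure of 2718 to reproduce is the larger problem. It does not remove this one: a repaired base calculation would carry the same omission.

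**Conclusion.** The point holds in a limited form. One sizing input has two time frames, and the printed inputs ignore a delay that the trial's own schedule builds in. The assertion that they reflect actual risk exposure is therefore unsupported on the page.

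Timing alone moves a nominal 80% to about 71-73% with no late detection or with equal late detection. It gives about 78-80% with 3 points late in control and 1 in intervention, and about 78-86% with late detection in control only. These figures are illustrative. They rest on constant hazards, treatment at months 1 and 4, a patch-2 share of 20-35%, and scaling to the printed 80%. That the sign depends on the meaning of 19% is the main reason to settle that meaning.

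The delay should not be offered as the explanation for the trial's power shortfall: with immediate treatment the printed inputs already give only about 46-72% at 2718, depending on method.

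**What to change.** 1. Give 19% one definition and use it in both the Sample size text and Table 2. State the expected yield of the two recordings and the later detection separately, and do the same for control's 6%.
2. First restore a base calculation that reproduces its own N from the printed inputs under three years of fixed follow-up.
3. On that base, re-run power at the planned N with time-dependent treatment start in both arms: the 17% yearly risk before anticoagulation and 7.3% after, with patch 1 at about month 1, patch 2 at month 3 to 5, and usual-care detection spread over follow-up. Include a higher early hazard as a sensitivity case only.
4. Print the resulting power in place of 80%, and remove or qualify the statement about actual risk exposure.

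The cost is one re-run and a few lines of text. The stated power will probably be lower. No patients are added and trial conduct does not change.
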